## Abstract

**Background::**

Acupuncture has a long history in China and is currently widely used in clinical practice. However, there is no large sample data confirming the effectiveness of acupuncture in treating stroke and its sequelae. This article presents a study protocol for a multicenter, randomized, controlled trial for evaluating the efficacy of acupuncture in treating post-stroke dysphagia.

**Methods/design::**

A randomized controlled trial will be conducted in three hospitals in Heilongjiang, Changchun, and Beijing. A total of 252 patients with post-stroke swallowing ability will be randomly divided into two groups; specifically, the experimental group, which will receive acupuncture treatment, and the control group, which will undergo rehabilitation training for 2 weeks. The main results will be evaluated using the standard swallowing function scale, videofluoroscopic swallowing examination, and functional magnetic resonance imaging. The secondary observation indexes will include surface electromyography signal analysis and the modified Barthel index. Measurements will be obtained before treatment, as well as 1 week, 2 weeks, and 1 month after treatment.

**Discussion::**

This trial could clarify the effectiveness of acupuncture in stroke; moreover, it will determine whether acupuncture can improve swallowing function.

**Trial registration::**

Chinese Clinical Trial Registry (ChiCTR), ChiCTR2000030994.

## Introduction

1

Stroke, which is also known as cerebral apoplexy, is characterized by high morbidity, mortality, recurrence, and disability rates; moreover, it has the second-highest mortality rate worldwide.^[1,2]^ The increasing stroke incidence in the young population is a significant public health issue. Moreover, the stroke burden has been increased by general population growth and the increasingly aging population.^[3]^

Stroke can cause several sequelae, including motor dysfunction, sensory dysfunction, cognitive function, and swallowing dysfunction. Approximately 65% of patients with acute stroke present dysphagia.^[4]^ Post-stroke damage to the brain, cerebellum, or brain stem can impair swallowing function.^[5]^ Swallowing difficulties cause several problems, including aspiration and malnutrition, which can cause further complications. Among them, pneumonia is the main mortality cause in patients with stroke; moreover, there is a need to address socioeconomic issues, such as long-term medical expenses.^[6,7]^

There has been rapid development and progress in modern rehabilitation technology, swallowing training, transcranial magnetic stimulation, electrical stimulation, and other methods, which allow significant improvements in post-stroke swallowing disorders. Acupuncture is an important treatment method in traditional Chinese medicine for rehabilitation. It has a definite effect, simple and easy operation, and less toxicity and side effects. It is a common clinical method for stroke treatment, including scalp acupuncture, nape acupuncture, tongue acupuncture, body acupuncture, and other needle methods. Currently, there have been numerous acupuncture studies on stroke treatment, including post-stroke swallowing dysfunction. Numerous clinical reports have indicated that acupuncture can significantly improve swallowing function.^[8,9]^ However, there remains no high-quality and effective evidence clearly showing acupuncture-mediated recovery of stroke and swallowing disorders.^[10]^

Consequently, the proposed study will use commonly used rating scales, surface electromyography (sEMG) signals, and functional magnetic resonance imaging (fMRI) to examine the acupuncture efficacy in the treatment of swallowing dysfunction in patients with stroke.

## Methods/design

2

### Objectives

2.1

The study objective is to formulate a TCM acupuncture rehabilitation program for post-stroke dysphagia (oral and pharyngeal stages). The central regulation mechanism underlying dysphagia treatment using TCM rehabilitation will be analyzed from the perspective of post-treatment brain function changes using resting fMRI and self-comparative analyses.

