### Study design

2.2

This will be a multicenter, randomized controlled study conducted at the Second Affiliated Hospital of Heilongjiang University of Traditional Chinese Medicine, Changchun University of Traditional Chinese Medicine, and China Rehabilitation Research Center from December 1, 2018, to December 31, 2021. Patients with post-stroke dysphagia who meet the inclusion criteria will be divided into the experimental and control groups using a central randomization system. The experimental and control groups will receive acupuncture treatment and conventional rehabilitation training, respectively. The primary results will be obtained using the standardized swallowing assessment (SSA), videofluoroscopic swallowing study (VFSS), and fMRI. The secondary observation indicators will include surface electromyography (sEMG) analysis and modified Barthel index (MBI). The follow-up indicators include stroke-specific quality of life scale (SS-QOL) and the SSA. Measurements will be obtained before treatment, as well as 1 week, 2 weeks, and 1 month after treatment. fMRI will be only performed in the subject unit. Forty-two participants will undergo pre- and post-treatment fMRI assessment to analyze the central regulatory mechanism underlying swallowing function remodeling in the rehabilitation program of TCM. Figure 1 and Table 1 present the technology roadmap and clinical observation flow charts, respectively.

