### Inclusive criteria

2.4

The inclusion criteria will be as follows: clinical diagnosis of first-episode unilateral cerebral hemisphere infarction or cerebral hemorrhage, with confirmation using CT or MRI; meeting the diagnostic criteria for dysphagia; showing abnormal expressions of the oral and pharynx stages upon VFSS evaluation; having stroke and dysphagia duration within 3 months; being conscious with stable vital signs and a mini-mental state examination score of ≥ 21; age 45 to 75 years; and having provided informed consent.

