#### Evaluation indexes

2.10.1

The primary outcome indicators will be the SSA and VFSS, while the secondary outcome indicators will be the sEMG signal analysis and MBI. The common evaluation index will be the SS-QOL while the follow-up indicators will be the SS-QOL and SSA.

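### Self-comparison is the only analysis named for the fMRI mechanism objective; in early stroke it cannot separate the acupuncture programme from natural recovery, and the arms of the 42 scanned patients are not stated

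*Protocol article*

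**What the plan says.** Section 2.1 (Objectives) sets a mechanism objective for the TCM programme and names its method: it will be studied "from the perspective of post-treatment brain function changes using resting fMRI and self-comparative analyses". Section 2.2 (Study design) supplies the sample: "Forty-two participants will undergo pre- and post-treatment fMRI assessment to analyze the central regulatory mechanism underlying swallowing function remodeling". It also restricts the site: "fMRI will be only performed in the subject unit". It gives no split of the 42 by arm and no between-arm fMRI comparison. Section 2.4 (Inclusive criteria) admits patients "having stroke and dysphagia duration within 3 months".

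The status of fMRI varies. The abstract states "The main results will be evaluated using the standard swallowing function scale, videofluoroscopic swallowing examination, and functional magnetic resonance imaging", and section 2.2 states "The primary results will be obtained using the standardized swallowing assessment (SSA), videofluoroscopic swallowing study (VFSS), and fMRI". Section 2.10.1 (Evaluation indexes) leaves it out: "The primary outcome indicators will be the SSA and VFSS". Table 1 has no fMRI row.

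The same trial has a centrally randomised control arm that receives conventional rehabilitation training, with 126 patients planned per arm.

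**The concern.** A within-patient change is the sum of everything that happens between two scans: any effect of the programme, spontaneous recovery, other care, and drift or familiarity from repeat scanning. Within 3 months of a stroke the recovery part may not be negligible. One group's before-after data hold nothing that separates these parts, and a larger sample only makes the mixed total more precise. The trial has a concurrent randomised arm that would share the recovery and repeat-scan parts, but the method named for this objective does not use it.

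At stake is the mechanism objective. If the stated method is followed and nothing is added, a significant fMRI change could be taken for the central mechanism of acupuncture when it is recovery alone. The SSA and VFSS comparisons are not affected.

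**Working it through.** **Inputs from the article.** 42 participants with scans before and after treatment (section 2.2); self-comparison as the method (section 2.1); stroke within 3 months (section 2.4); two randomised arms (section 2.2). The article gives no effect size, SD, alpha or power for the 42, so that number cannot be reproduced.

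**Assumptions.** The documents give no natural-recovery shift for any fMRI measure. Let d be the mean change from recovery and repeat scanning alone, in SDs of the change score, and take d = 0.1, 0.2, 0.3 and 0.5. The acupuncture effect is zero. Tests are two-sided at 5%. Because the split is not stated, two cases are shown: all 42 in one arm, or 21 in an arm.

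**Step 1: before-after test.** The paired t statistic has n − 1 degrees of freedom and noncentrality d × √n. The probability of significance is P(|T| > critical value), with critical value 2.020 for n = 42 and 2.086 for n = 21.

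| d (assumed) | d√42 | Significant, n = 42 | d√21 | Significant, n = 21 |
|---|---|---|---|---|
| 0.1 | 0.648 | 10% | 0.458 | 7% |
| 0.2 | 1.296 | 24% | 0.917 | 14% |
| 0.3 | 1.944 | 48% | 1.375 | 26% |
| 0.5 | 3.240 | 89% | 2.291 | 59% |

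These are not inflated type I error rates of the paired test. If recovery moves the measure, the test is right to reject no change. The table shows how often a real change would be open to wrong attribution to acupuncture.

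**Step 2: separate tests in each arm.** Suppose 21 are scanned in each arm, both arms change by the same d, and each arm is tested on its own. Exactly one arm is significant with probability 2p(1 − p), where p is the n = 21 figure above. For d = 0.3 this is 2 × 0.258 × 0.742 = 38%; for d = 0.5 it is 2 × 0.587 × 0.413 = 48%. Significance in one arm but not the other is therefore no evidence that the arms differ.

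**Step 3: between-arm test.** Recovery and repeat-scan effects that both arms share cancel in the difference, so the test of no difference stays at 5% whatever d is. For 21 per arm, the normal approximation gives a detectable difference at 80% power of (1.960 + 0.842) × √(2/21) = 0.86 SD. The exact two-sample t with 40 degrees of freedom gives about 0.89 SD.

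**The case against.** The strongest reply is that the uncontrolled reading is inferred. The article does not say that self-comparison is the only fMRI analysis. It places fMRI among the main or primary results of a two-arm randomised trial, and the introduction says it serves to examine acupuncture efficacy. Figure 1 might show the split and is not available here. A third party is to write the statistical analysis plan, and a condensed article need not give the full fMRI model. It follows that a between-arm fMRI comparison is not excluded. The point still stands, because the objective itself names a method, and that method cannot deliver the attribution sought.

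A reader might go further. Section 2.9.1 gives 84 cases and lists the three centres; 3 × 84 = 252, so 84 is the number per centre and half of it is 42. From this one might infer that only the acupuncture arm is scanned. The documents do not support that: 42 fits equally well with 21 per arm, or with any half of one centre's patients.

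It can also be said that before-after analysis is a legitimate description of change, and that no passage commits to a causal claim from a significant paired test. That is fair. The trouble begins only when the change is offered as the mechanism of the programme, which is how the objective is framed.

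Finally, the control is active swallowing training, so a between-arm contrast is no clean test of whether acupuncture has a central effect. This limit is real and belongs with the remedy.

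**Conclusion.** The concern holds in a limited form. Self-comparison is the only analysis the article names for the fMRI mechanism objective, the arms of the 42 are not stated, and within-patient change this early after stroke cannot separate the programme from natural recovery and repeat-scan effects. That conclusion follows from the design and needs no assumed figure.

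The size does rest on assumptions. For recovery shifts of 0.1 to 0.5 SD and no acupuncture effect, a change open to wrong attribution appears in 10% to 89% of studies with 42 in one arm, and in 7% to 59% with 21. Neither range should be cited without the assumed shift and the assumed split. The documents do not show that the control arm goes unscanned, or that an uncontrolled claim will be reported. The point should be corrected, but it does not threaten the main comparison.

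**What to change.** 1. State how the 42 are split, and take them from both randomised arms at the scanning unit, for example 21 per arm.
2. Make the main fMRI analysis the between-arm difference in the post-treatment measure, adjusted for its baseline value.
3. Report within-arm change descriptively, and do not infer a difference from separate within-arm tests.
4. Label the fMRI analysis exploratory, and bring the abstract, section 2.2, section 2.10.1 and Table 1 into line with that.

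**Cost.** The total stays at 42 participants, so no extra scans are needed, although the number per arm falls if all 42 were meant for one arm. Power is modest: 80% only for a difference of about 0.89 SD with 21 per arm. The contrast estimates acupuncture versus training. A null result would not show that acupuncture has no central effect, because both treatments could produce the same change.

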### Study design

2.2

This will be a multicenter, randomized controlled study conducted at the Second Affiliated Hospital of Heilongjiang University of Traditional Chinese Medicine, Changchun University of Traditional Chinese Medicine, and China Rehabilitation Research Center from December 1, 2018, to December 31, 2021. Patients with post-stroke dysphagia who meet the inclusion criteria will be divided into the experimental and control groups using a central randomization system. The experimental and control groups will receive acupuncture treatment and conventional rehabilitation training, respectively. The primary results will be obtained using the standardized swallowing assessment (SSA), videofluoroscopic swallowing study (VFSS), and fMRI. The secondary observation indicators will include surface electromyography (sEMG) analysis and modified Barthel index (MBI). The follow-up indicators include stroke-specific quality of life scale (SS-QOL) and the SSA. Measurements will be obtained before treatment, as well as 1 week, 2 weeks, and 1 month after treatment. fMRI will be only performed in the subject unit. Forty-two participants will undergo pre- and post-treatment fMRI assessment to analyze the central regulatory mechanism underlying swallowing function remodeling in the rehabilitation program of TCM. Figure 1 and Table 1 present the technology roadmap and clinical observation flow charts, respectively.

**Figure 1 F1:**
[figure not shown]
Present the technology roadmap.

**Table 1 T1:** Clinical observation flow charts.

Research stage	Selection period	Treatment period		Follow-up period
Evaluation times	First time	Second	Third time	Fourth
Evaluation time point	1 and 0 days before treatment	1 week after intervention	2 weeks after intervention	1 month after the end of the intervention
Inclusion criteria	•			
Exclusion criteria	•			
Informed consent form	•			
Online random grouping	•			
General assessment				
General information	•			
Current medical history/allergic history	•			
Past history/complications	•			
Evaluation of the curative effect index				
VFSS	•		•	
SSA	•	•	•	•
Surface electromyography signal	•	•	•	
Improved Barthel index	•	•	•	
SS-QOL				•
Security assessment				
Life indication	•	•	•	•
Other assessments				
Adverse reactions/events		•	•	
Recurrence situation				•
Treatment compliance			•	

SSA = standardized swallowing assessment, SS-QOL = stroke-specific quality of life scale, VFSS = videofluoroscopic swallowing examination.

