#### Evaluation time

2.10.2

Measurements will be obtained before the intervention, 1 week after intervention, and 2 weeks after intervention. The follow-up time point will be 1 month after the end of the intervention.

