## Discussion

3

Dysphagia refers to swallowing dysfunction.^[11]^ Clinical patients are commonly in the oral, pharyngeal, or both stages. The mouth stage is the chewing food process to form a bolus, with the tongue moving the bolus back and forth before entering the pharynx. Dysfunction involves weakness of the facial muscles, including the chewing, labial, and tongue muscles, which impedes food bolus formation and smooth delivery to the pharynx. The pharyngeal stage refers to the process of the food bolus entering the oropharynx into the esophagus. This stage involves abnormal pharyngeal muscle and laryngeal function, which often causes aspiration, pharynx retention, and hoarseness.^[12]^

The SSA is divided into three parts: clinical examination, observation of patients swallowing 5 mL of water, and observation of patients swallowing 60 mL of water. It has a total score of 46, with the lowest possible score being 17. A higher cumulative score of each item indicates worse swallowing function. Some studies have reported that SSA is more feasible and suitable for evaluating dysphagia.^[13]^ The SSA includes 10 items divided into four levels: independent, less dependent, moderately dependent, and completely dependent. The VFSS allows dynamic assessment of the swallowing function of the mouth, pharynx, and upper esophagus using TV fluoroscopy. The VFSS is considered the “gold standard” for evaluating swallowing function. It is widely used for the comprehensive evaluation of the patients’ oral, pharyngeal, and esophageal swallowing conditions.^[14]^ The sEMG allows evaluation of the physiological process of swallowing. It is a simple and reliable screening that allows preliminary identification of dysphagia and has advantages of accuracy, rapidity, and non-invasiveness.^[15]^ fMRI is a safe, non-invasive, and non-radiation imaging method with high temporal and spatial resolution. Anatomical and functional images can be simultaneously obtained in a single imaging session.^[16]^

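### Table 1 schedules adverse-event recording at weeks 1 and 2 only and leaves the existing 1-month visit blank, so late events in patients who still attend are not systematically recorded

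*Protocol article*

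**What the plan says.** Table 1 sets out four evaluations: baseline, 1 week, 2 weeks, and a follow-up visit. The text on evaluation time (section 2.10.2) confirms the last of these: "The follow-up time point will be 1 month after the end of the intervention". The abstract gives the length of treatment: "rehabilitation training for 2 weeks".

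The row "Adverse reactions/events" carries a mark at the second and third evaluations and none at the fourth. Four other rows are marked at the fourth: SSA, SS-QOL, vital signs (labelled "Life indication") and a recurrence item that is not defined further. Section 2.10.1 agrees for efficacy: "the follow-up indicators will be the SS-QOL and SSA".

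The Introduction lists aspiration and malnutrition among the problems caused by impaired swallowing, and adds that "pneumonia is the main mortality cause in patients with stroke".

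**The concern.** The trial brings patients back a month after treatment to measure swallowing, which is a primary outcome domain, and quality of life. The same schedule does not ask at that visit what adverse events have occurred since week 2. Aspiration and pneumonia are complications that the article itself connects with dysphagia, and they can arise after a two-week course has finished.

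If the schedule is followed as printed, the safety comparison between arms rests on the treatment period, while the efficacy comparison extends a month further. The interventions differ in kind: needling of the neck and tongue in one arm, and exercises, with feeding training for pharyngeal-stage patients, in the other. Equal late harm should therefore be shown and not presumed. Events that are not asked about at the visit may be hard to recover afterwards.

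**Working it through.** This is a check of the schedule. No sample size, power or significance level enters, and the article states no figure to reproduce.

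**Step 1. Is the blank cell real?** Tables read from PDF can lose marks. Here the SSA, SS-QOL, vital-sign and recurrence rows all keep their mark in the fourth column, so that column was read correctly. The adverse-event row has its two marks under weeks 1 and 2.

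**Step 2. Is the patient assessed in person at 1 month?** Yes. The Discussion describes the SSA as "clinical examination, observation of patients swallowing 5 mL of water, and observation of patients swallowing 60 mL of water". That cannot be done by letter or telephone, and vital signs are also marked. No new visit is needed to ask about adverse events.

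**Step 3. Does any other text extend the recording?**

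- Section 2.10.1 names only SS-QOL and SSA as follow-up indicators.
- Section 2.10.2 gives the date of the visit but not its safety content.
- Section 2.7 deals with patients discontinued during the trial and carries their last result into the efficacy and adverse-reaction analysis. It sets no 1-month collection.
- Section 2.6 requires staff to contact drop-outs and enter the reason in the case report form. This reaches patients who leave, including those who leave because of a severe reaction or complication. It does not reach patients who stay.

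**Step 4. What is captured after week 2, and what is not?**

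| Late event | Scheduled place of record |
|---|---|
| Event that leads to drop-out | Drop-out reason, section 2.6 |
| Recurrence | Recurrence row, fourth evaluation |
| Abnormal vital signs on the day | Vital-sign row, fourth evaluation |
| Pneumonia or aspiration event, resolved or ongoing, in a patient who attends | None |
| Readmission, in a patient who attends | None, unless it falls under recurrence |

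**Step 5. How long is the uncovered interval?** Inputs: 14 days of treatment (abstract), and a follow-up month of m days, assumed to be 28 to 31 because the article does not define it. The week-2 evaluation is taken as the end of treatment, since Table 1 places it in the treatment period.

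Share after the last scheduled adverse-event record = m / (14 + m):

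- m = 28: 28/42 = 67%
- m = 30: 30/44 = 68%
- m = 31: 31/45 = 69%

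With the fourth cell marked, the schedule would cover the whole 42 to 45 days instead of the first 14.

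**The case against.** The strongest reply is that the marked cells cover the whole exposure. Both interventions end at week 2, and recording adverse events over the treatment period is a coherent choice that contradicts nothing else in the article. A journal article also commonly leaves adverse-event definitions, serious-event reporting and the follow-up of ongoing events to the full protocol, which is not shown. This stands in part. It makes the point an improvement to the schedule and not an error that invalidates the trial. It does not remove the point, because the article prints a visit-by-visit schedule, and that schedule fixes adverse-event recording at two visits.

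A reader might infer more from the blank cell than the article supports:

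- **That all harm follow-up stops at 2 weeks.** It does not. Vital signs, listed under the table's safety heading, and recurrence are both marked at 1 month.
- **That missing 1-month SSA values would go unexplained.** Section 2.6 requires drop-out reasons to be obtained and recorded, and is not limited to the treatment period.
- **That pneumonia is the event the treatment is meant to prevent.** The objectives and outcome sections do not say so. Pneumonia appears in the Introduction as background on stroke patients, and it is not an endpoint.
- **That about two thirds of harm is missed.** The 67% to 69% is a share of calendar days after treatment has ended. No event rate is given for that interval, so it cannot be turned into a number or share of events. Nor would all 252 planned patients necessarily be affected, since the sample size section itself allows for 30% loss and exclusion.

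**Conclusion.** The point holds in a limited form. As printed, the schedule has no systematic record of adverse events, such as pneumonia or aspiration, arising between week 2 and the 1-month visit in patients who still attend. Drop-out reasons, vital signs and the recurrence item capture some late harm but not these events.

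The interval is about two thirds of post-baseline calendar time (28/42 to 31/45). This assumes a 14-day treatment period ending at the third evaluation and a month of 28 to 31 days. How many events fall in the interval cannot be derived from the article. The effect is on the completeness of the safety comparison; the efficacy analysis and the sample size are untouched. The change is worth making because it is specific and cheap. The conclusion would change only if the full protocol already schedules adverse-event recording at 1 month, in which case Table 1 should be brought into line with it.

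**What to change.** In Table 1, mark the adverse-event row at the fourth evaluation and state that the record covers the whole interval since week 2, in both arms. Ask by name about pneumonia, readmission and death, along with an open question for other events. State that adverse events will be reported by arm over the full period from the start of treatment to the 1-month visit, preferably with the treatment and follow-up periods also shown separately.

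The cost is one extra case report form page at an existing visit, with the data entry that goes with it. No visit, treatment, sample size or primary analysis changes.
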